#### Statistical Analyses

Where feasible and appropriate, multiple imputation will be used to account for missing data [60]. Multilevel random effects models (MRMs) will also be used to account for correlated data (dialysis center clustering and serial measurement). We will compare the characteristics of patients who refuse to join the study or are never successfully contacted to those who do not, as well as patients who drop-out to those who do not, to determine if the patient selection procedure has biased the sample.

We will compare the difference in mean knowledge change, change in self-efficacy, and change in decisional balance (baseline to follow-up survey) of participants in the 3 study arms using MRMs with normal outcome distributions. A MRM with a normal outcome distribution will also be used to test for mean differences in the Decisional Conflict Scale at 8 months post-baseline, and Rao-Scott χ^2^ tests adjusting for dialysis center clustering will be performed to test for differences in patients’ answers to the informed decision-making items on the follow-up survey: “I have all the facts I need to make an informed decision about whether to stay on dialysis/pursue DDKT/pursue LDKT” (agree/disagree). Rao-Scott χ^2^ tests will also be used to test differences in the proportion of patients in each condition who took each small step toward transplant (e.g., “Do you plan to share your interest in living donation with your family and friends?”), operationalized as the number who had not taken each step at baseline but had at follow-up.

The heterogeneity of treatment effect will be tested using interactions between the educational condition patients are assigned to and their demographic, psychosocial, and clinical characteristics (e.g., race, level of SES vulnerability, medical mistrust, health literacy), examining differences in changes in these groups' transplant knowledge, decisional balance, self-efficacy, small steps toward transplant, and informed decision-making using MRMs. These models will determine whether the *ETH* educational conditions are more or less effective for patients who: (1) have different SES barriers, (2) different levels of health literacy and medical mistrust, and (3) are Black or White. Finally, we will explore the impact of the text messages by comparing all study outcomes between patients who did and did not enroll in the texting program, stratified by whether the patient was randomized to the *ETH*-EG or *ETH*-PG condition, using MRMs.

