### RCT Overview

This RCT has three conditions with equal allocation of patients to each condition: (1) the control condition or standard-of-care; (2) the *ETH* Patient-Guided (*ETH*-PG) condition; and (3) the *ETH* Educator-Guided (*ETH*-EG) condition (Fig. 2). All enrolled patients will complete a baseline survey and a follow-up survey, 8 to 10 months post-baseline. We will recruit 540 patients at the start of the 8 month educational intervention period to complete the baseline survey, with 180 patients in each condition. After attrition, 150 patients in each condition (*n* = 450 total) are expected to complete the follow-up survey.

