### Patient Recruitment Eligibility, and Retention

The sample for our study will be drawn from the MoKP patient roster plus additional patients from Missouri dialysis centers. To enroll in the RCT each subject must: (1) be 18–74 years of age, (2) self-identify as Black or White race, (3) currently be on dialysis, (4) have a household income at or below 250 % of the federal poverty level, and (5) be able to speak and read in English. Participants who meet any of the following exclusion criteria are not enrolled: (1) has a visual and/or hearing impairment that would preclude him/her from watching and reading educational study materials, (2) has had a previous kidney transplant, and/or (3) has previously been told that they are not a candidate for transplant.

Those who are transplant-eligible will be contacted directly by phone and via mailed letters, inviting them to participate in our trial. Additionally, Kilgore’s Pharmacy, contracted by the University of Missouri Health System to support patients who receive medication assistance through MoKP, will insert flyers advertising the *ETH* research study into patients’ prescription medication refills. After being informed of the risks and benefits of the trial, patients will be asked to give verbal informed consent to participate. If a patient agrees to participate, he or she will be randomized to one of the three educational conditions using an unrestricted (simple) random allocation sequence implemented within the trial’s data capture software, after they complete the baseline survey. The randomization sequence was created by a data manager using a random sequence generator, is stored in an encrypted spreadsheet, and is not accessible by the principal investigator. This protocol has been approved by the University of California, Institutional Review Board (#14-000802), the University of Missouri, Columbia Institutional Review Board (#00048966), and is registered at ClinicalTrials.gov (#NCT02268682).

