### Survey Timepoints

#### Baseline Survey

Patients will complete a short phone screening (5 min.) to assess whether they meet the eligibility criteria and if so, are invited to participate, review the informed consent sheet with a surveyor, and then complete a 45-minute baseline survey. The survey assesses demographic, clinical and cultural factors, socioeconomic transplant derailers, baseline level of transplant knowledge, decisional balance, self-efficacy, and any steps they may have taken to learn about staying on dialysis, DDKT or LDKT. Patients will receive $25 for completing the baseline survey.

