### Outcomes

#### Transplant Knowledge

Our primary outcome measure is level of DDKT and LDKT knowledge. Patients will be asked 17 true/false and 8 multiple choice questions about the basic facts, advantages, risks and outcomes of DDKT and LDKT to assess knowledge levels (e.g., “Transplant recipients are at risk of developing high blood pressure and high cholesterol,” “The transplant team will let a living donor back out from donating on the day of the surgery”).

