#### Power and Sample Size

Power analyses were based on changes in transplant knowledge, our primary study outcome. The study design and analyses were treated as a test of the differences in mean knowledge score change between patients in the *ETH*-PG, *ETH*-EG, and Control conditions, 8–10 months post-baseline. Power calculations were based on the number of dialysis centers per condition, the number of individuals per dialysis center, the expected intra-class correlation, and the estimated variability of the outcome variable [59]. Based on the original *ET* trial [19], we estimated that a mean knowledge change score of 2.0 points would be needed to detect a significant difference between patients receiving standard-of-care, *ETH*-PG, and *ETH*-EG. It was assumed that patients coming from the same dialysis centers would have correlated knowledge scores. Since we are examining 3 conditions, a Bonferroni correction was required to adjust the Type 1 α for comparison of 3 group means (0.05/3 = 0.017). Based on these assumptions, we calculated that a design of 150 patients per condition, 450 patients total, will be required to find a mean change of 2.0 points in knowledge between groups at 90 % power. Expecting an approximately 20 % attrition rate over time, we are oversampling (180 patients per condition) to ensure that we have sufficient power to be able to assess our primary endpoint at the completion of the study period.

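### Knowledge, self-efficacy and decisional balance are compared as change scores, although adjusting for the baseline score already collected would be more precise and would remove chance baseline imbalance

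*Protocol article*

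**What the plan says.** The primary outcome is knowledge: "Our primary outcome measure is level of DDKT and LDKT knowledge" (Transplant Knowledge). Under Statistical Analyses the arms are compared on change from baseline: "We will compare the difference in mean knowledge change, change in self-efficacy, and change in decisional balance (baseline to follow-up survey) of participants". Power and Sample Size describes the primary test in the same terms, as "a test of the differences in mean knowledge score change between patients" in the three conditions.

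The model class is given as follows: "Multilevel random effects models (MRMs) will also be used to account for correlated data (dialysis center clustering and serial measurement". There are two waves only: "All enrolled patients will complete a baseline survey and a follow-up survey" (RCT Overview). The Baseline Survey section lists "baseline level of transplant knowledge, decisional balance, self-efficacy" among what is measured, and allocation follows completion of that survey, "using an unrestricted (simple) random allocation sequence" (Patient Recruitment Eligibility, and Retention).

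The article does not say that the baseline value of an outcome enters its model, or that baseline means are constrained to be equal. The sections under Predictors and Covariates cover demographic, clinical and cultural factors, socioeconomic derailers, prior transplant education and health literacy. Baseline outcome scores are not among them.

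**The concern.** A change score fixes the coefficient on baseline at 1. When the correlation between the two surveys is below 1 and variances are similar, that coefficient is too large. It carries baseline noise into the outcome and over-corrects for any chance difference between arms at baseline: through regression to the mean, an arm that happens to start lower appears to gain more.

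Two things are at stake. Precision on the primary outcome is given up although the data needed to keep it are already collected. And in any single realisation of the trial, an observed baseline difference moves the estimated effect. Simple randomisation, with no stratification, leaves the size of that difference to chance and sample size.

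**Working it through.** **Inputs from the protocol article.** Target difference 2.0 points; power 90%; alpha 0.05/3 = 0.0167 per comparison (printed as 0.017); 150 analysable patients per arm; 180 recruited per arm; attrition about 20%.

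**Inputs not given.** The SD of change, the intra-class correlation and the center size are named as inputs without values, and rho is not mentioned. The test is taken as two-sided. The figure of 150 per arm therefore cannot be reproduced independently; it can only be solved backwards.

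**Step 1: SD implied by the plan.** From n = 2·SD²·(z₁₋α/₂ + z₀.₉)²/δ²:

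SD = 2.0·√(150/2)/(2.394 + 1.282) = 4.71 points.

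This is an effective SD of change with any clustering inflation included. By construction it returns 150 per arm at 90% power. The standard error of an arm difference is 4.71·√(2/150) = 0.54 points.

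**Step 2: variance ratio.** With the same variance s² at both surveys:

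- Var(change) = 2s²(1−rho)
- Var(baseline-adjusted) = s²(1−rho²)
- Ratio = (1+rho)/2

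The ratio is below 1 for every rho below 1. If the SDs differ (s₀ at baseline, s₁ at follow-up), the change-score variance exceeds the adjusted variance by (s₀ − rho·s₁)², which cannot be negative. A simulation of 20,000 two-arm trials at each of rho 0.3, 0.5 and 0.7 gave ratios of 0.657, 0.753 and 0.848, against 0.65, 0.75 and 0.85 from the formula. Both estimators were unbiased.

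**Step 3: power and sample size after adjustment.** The SD becomes 4.71·√((1+rho)/2). The 144 column is 180 × 0.80, the number left after the stated attrition.

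| Assumed rho | Variance ratio | SE at 150 per arm | n per arm for 90% power | Power at 150 | Power at 144 |
|---|---|---|---|---|---|
| Change score | 1 | 0.54 | 150 | 90.0% | 88.6% |
| 0.3 | 0.65 | 0.44 | 98 | 98.5% | 98.1% |
| 0.4 | 0.70 | 0.46 | 105 | 97.7% | 97.2% |
| 0.5 | 0.75 | 0.47 | 113 | 96.8% | 96.1% |
| 0.6 | 0.80 | 0.49 | 120 | 95.7% | 94.9% |
| 0.7 | 0.85 | 0.50 | 128 | 94.4% | 93.5% |
| 0.8 | 0.90 | 0.52 | 135 | 93.1% | 92.0% |
| 0.9 | 0.95 | 0.53 | 143 | 91.6% | 90.3% |

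**Step 4: shift from chance imbalance.** The score SD is s = 4.71/√(2(1−rho)). A baseline difference of 1.96 standard errors is 1.96·s·√(2/150), and the change-score estimate moves by (1−rho) times that.

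| Assumed rho | Baseline difference (points) | Shift in estimate (points) | Shift as share of 2.0 |
|---|---|---|---|
| 0.3 | 0.90 | 0.63 | 32% |
| 0.5 | 1.07 | 0.53 | 27% |
| 0.7 | 1.38 | 0.41 | 21% |

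**Step 5: does a mixed model already solve this?** One simulated three-arm data set with two complete waves (rho 0.5, unit SD, 150 per arm) was fitted four ways. A mixed model with arm, time and their interaction gave the same arm-by-time estimates as the change-score model, and the same standard error, 0.1154. Adjustment for baseline gave 0.099, and a mixed model with a common baseline mean gave 0.100. A multilevel model for serial measurement therefore does not supply baseline adjustment unless the common-baseline constraint is specified.

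**The case against.** The strongest reply is that the article names multilevel models without listing their fixed effects. A model with a common baseline mean is itself a multilevel model for serial measurement, and it estimates a between-arm difference in mean change. The planned sentence does not rule it out, and a full analysis plan might specify it. It is true that the parameterisation is open. But both the power section and the analysis section describe a comparison of mean change, and the ordinary two-wave arm-by-time model reproduces the change-score contrast.

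Second, the planned test is not wrong. Over repeated randomisation the change-score contrast is unbiased, and its standard error already reflects chance imbalance. The power section and the analysis also use the same contrast. All of this stands: the loss is in precision, together with bias conditional on an observed imbalance, not in validity.

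Third, the size rests on an assumed rho and a back-solved SD. At rho 0.8 the gain is about 3 points of power. That also stands, although the direction does not depend on the assumption.

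Fourth, 180 recruited per arm already makes a large imbalance unlikely: a difference beyond 1.96 standard errors arises in about 1 in 20 comparisons. That is fair, and the shifts in the second table should be read as what an unlucky draw would do.

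Finally, the article does not rank its secondary outcomes, and the Decisional Conflict Scale, compared at follow-up only, is unaffected.

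**Conclusion.** The concern holds. The article commits the primary outcome, and self-efficacy and decisional balance with it, to a comparison of mean change that is valid but avoidably imprecise. If the plan's own 90% at 150 per arm is taken at face value, baseline adjustment brings power to between 95.7% and 97.7% for rho from 0.4 to 0.6, and to 93.1% at rho 0.8. At the 144 per arm that 20% attrition from 180 would leave, change-score power is 88.6%; adjustment gives 97.2%, 96.1% and 94.9% at rho 0.4, 0.5 and 0.6, and still 90.3% at rho 0.9. The gain therefore more than covers that shortfall.

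These figures assume a two-sided test, equal variance at the two surveys, an effective SD of change of 4.71 solved from the stated sample size, the same clustering inflation under both analyses, and the rho values shown. The change should be made, but the planned analysis would not be invalid without it.

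**What to change.** State that knowledge (primary), self-efficacy and decisional balance are each analysed at follow-up in a multilevel model with condition, the baseline value of the same score and a random intercept for dialysis center. Alternatively, specify a two-wave longitudinal model in which all arms share one baseline mean. With complete data the two give nearly the same answer; the second also keeps patients who have only a baseline survey. Race can be added as a covariate, but the gains shown here come from the baseline score alone. The heterogeneity models for these three scores should follow the same form.

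The effect remains a between-arm difference in points, so the 2.0-point target and the sample size can stay as they are. The cost is a change of analysis wording, best recorded before outcome data are examined. No further data are needed.

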#### Small Steps toward DDKT and LDKT

Several action steps toward pursuit of both DDKT and LDKT will be assessed using validated measures (e.g., “Do you plan to call the transplant center to begin evaluation,” “Do you plan to share your interest in living donation with your family and friends?”) [50, 51], each of which the patient will report as having “already done,” “planning to do,” or “don’t plan to do.”

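### The test for each small step cannot use the baseline planning / not-planning answer, so a valid comparison gives up some precision

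*Protocol article*

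**What the plan says.** All references are to the protocol article.

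- **Statistical Analyses, main comparison of small steps.** Rao-Scott chi-square "tests will also be used to test differences in the proportion of patients in each condition who took each small step toward transplant", with a step taken "operationalized as the number who had not taken each step at baseline but had at follow-up". No covariate is named.
- **Small Steps toward DDKT and LDKT.** Several steps are asked about, "each of which the patient will report as having" one of three states: done, planned, or not planned.
- **Baseline Survey.** It covers "decisional balance, self-efficacy, and any steps they may have taken to learn about staying on dialysis, DDKT or LDKT". Together with the endpoint definition, this implies that the step questions are asked at baseline.
- **Statistical Analyses, heterogeneity paragraph.** Interactions are examined for outcomes that include "self-efficacy, small steps toward transplant, and informed decision-making using MRMs", so multilevel models (MRMs) are already planned for the same outcome.
- **Statistical Analyses, informed-decision items.** Rao-Scott "tests adjusting for dialysis center clustering will be performed to test for differences" in the "informed decision-making items on the follow-up survey". The Baseline Survey section does not list these items, although the Abstract speaks of change in informed decision making.
- **Statistical Analyses, missing data.** "Where feasible and appropriate, multiple imputation will be used to account for missing data". No outcome is excluded.

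**The concern.** Among patients who have not yet taken a step, those planning it at baseline should be more likely to have taken it 8 to 10 months later than those who are not. The program's own foundation, a stage-based model of behavior change, says as much. A chi-square on the arm-by-outcome table merges the two groups, so the difference between them stays in the error variance of the arm comparison. A model that includes the baseline answer would remove it.

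What is at stake is precision on the outcomes closest to patient behavior. The trial is sized on knowledge and states no power for the steps, so avoidable variance here makes a real effect easier to miss. Type I error is not in question.

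**Working it through.** **The plan's own figure.** There is none to reproduce. The only stated power (90%, 150 per condition, alpha 0.05/3 = 0.017) is for the knowledge score.

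**Inputs.** From the article: 150 expected completers per arm. Assumed, because the article is silent:
- 75% of completers have not done the step at baseline: 0.75 × 150 ≈ 112 at risk per arm.
- Half of these are planning the step.
- The treatment odds ratio is 2.0 in both groups.
- One pairwise comparison at two-sided 0.05.
- Control step rates for planning / not planning are varied.

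**Formulas.** Let c₁, c₂ be the control rates (planning, not planning) and t₁, t₂ the intervention rates, where t = 2c/(1 + c). Let p_C and p_T be the arm averages, d = p_T − p_C, and n = 112.

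- Unadjusted: V_u = [p_C(1−p_C) + p_T(1−p_T)]/n
- Adjusted (standardised over the baseline answer): V_a = {½[c₁(1−c₁) + t₁(1−t₁)] + ½[c₂(1−c₂) + t₂(1−t₂)]}/n + ¼[(t₁−c₁) − (t₂−c₂)]²/(2n)
- Power = Φ(d/√V − 1.960)

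**One case in full, 45% / 10%.**
- t₁ = 0.6207, t₂ = 0.1818; p_C = 0.275, p_T = 0.4013; d = 0.1263.
- nV_u = 0.1994 + 0.2402 = 0.4396; standard error √(0.4396/112) = 0.0627.
- nV_a = 0.2415 + 0.1194 + 0.0010 ≈ 0.3618; standard error √(0.3618/112) = 0.0568.
- Variance ratio 0.3618/0.4396 = 0.82. The unadjusted test would need 1/0.823 = 1.22 times as many patients for the same precision.
- Power: Φ(2.015 − 1.960) = 52% unadjusted and Φ(2.221 − 1.960) = 60% adjusted.

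**All three cases**, with a simulation of 3,000 trials each (chi-square against logistic model):

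| Control rates, planning / not planning | d | V_a/V_u | Power, formula | Power, simulation |
|---|---|---|---|---|
| 30% / 15% | 0.136 | 0.96 | 62% → 64% | 61% → 62% |
| 45% / 10% | 0.126 | 0.82 | 52% → 60% | 53% → 60% |
| 50% / 5% | 0.106 | 0.70 | 40% → 53% | 39% → 52% |

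The simulated size with no effect (control rates 35% / 8%) was 0.046 for both methods, so both tests are valid. With 0.05/3 in place of 0.05 (critical value 2.394), the formula gives 45% → 47%, 35% → 43% and 24% → 36%.

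**Sensitivity to the inputs.** With 150 at risk per arm and two-sided 0.05, power goes from 0.78 to 0.80 (30% / 20%), 0.73 to 0.78 (40% / 15%), 0.61 to 0.72 (50% / 10%) and 0.42 to 0.62 (60% / 5%). The pattern is the same: the gain follows how well the baseline answer predicts the step.

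**Limits.** These calculations contain no center effect and no imputation. Leaving out the center effect should matter little: patients are randomised individually, and 450 patients over 160 centers is about 2.8 each. The simulated Rao-Scott correction averaged 0.99 to 1.00 for intra-class correlations of 0.05 to 0.20.

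**The case against.** The strongest reply is that nothing here is wrong. An unadjusted comparison of randomised arms is legitimate, knowledge is the primary outcome, the Background says that action steps will be explored, and every rate above is assumed. At the weak end the gain is 1 or 2 points. All of this stands, and it is why the point is modest. It does not remove the point, because the article names a test that takes no covariate when a suitable one appears to be in hand.

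The baseline planning answer is itself an inference. The three-state scale is given without a time point, and the Baseline Survey section mentions only steps taken. But a step not taken at baseline can be identified only if the question is asked then, so collection is likely.

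Stronger readings that the article does not support:

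- **That the test ignores baseline readiness or is wholly unadjusted.** Baseline done / not-done status is part of the endpoint, and the test adjusts for center clustering. Only the finer planning answer goes unused.
- **That the analysis rests on completers.** Multiple imputation is planned where feasible and appropriate, and these outcomes are not excluded. Proportions and their differences can be pooled across imputations.
- **That no effect size will be given.** Proportions are compared by arm, so a difference follows directly, and an article may leave the reported estimate to the full plan.
- **That the clustering correction is a fault.** A factor near 1 shows that it is harmless.
- **That MRMs for interactions contradict the main test.** They do not; they show only that the model family is already in use.
- **That the informed-decision items have the same gap.** No baseline value of these items is listed, so there is no matching answer to adjust for.

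**Conclusion.** The point holds as one of efficiency for the small-step comparisons. The planned test is valid but cannot use the baseline planning / not-planning answer. Under the assumptions of 112 at risk per arm, half planning, and odds ratio 2.0 at two-sided 0.05, adjustment adds about 1 to 13 points of power, with a variance ratio of 0.96 to 0.70. Where a given step falls in that range depends on how strongly the baseline answer predicts taking it, and the documents give no rates to settle this. The conclusion also assumes that the three-state answer is recorded at baseline. No bias and no error in the stated test has been shown.

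**What to change.** In the Statistical Analyses section, make the main comparison for each small step a logistic model:

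- **Population:** patients who had not taken the step at baseline. The present wording leaves open whether the others stay in the denominator; this settles it.
- **Terms:** arm, the baseline planning / not-planning answer, and an allowance for center, within the MRM family already planned for heterogeneity.
- **Report:** each pairwise contrast as a standardised risk difference with its confidence interval, combined over the planned imputations.
- **Sensitivity:** Rao-Scott may stay as a check.

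State also that the three-state step answer is recorded at baseline.

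For the informed-decision items, adjusting for baseline knowledge, prior transplant education and health literacy is optional. If those items are in fact asked at baseline, as the Abstract may suggest, the baseline answer is the natural covariate.

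Cost: a few sentences and a little programming, with no new data. The drawbacks are slightly more modelling and an odds ratio that is conditional on the covariates; reporting the standardised risk difference avoids the latter.

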#### Text Messaging

Text messaging has become a popular form of communication [41] and a common way to receive updates and important information quickly and conveniently [42]. Healthcare providers are now utilizing these short messages to deliver reminders to patients about appointments, prescription medications, and health education [43, 44]. In the United States, 89 % of households have access to a cell phone [45]. In 2011, 73 % of those who owned cell phones used them to send and receive text messages [46]. Thus, to increase the ways we can reach patients with educational messages, the *ETH* program has incorporated the use of text messages that contain recommendations, quiz questions, and educational facts that complement the printed materials and videos during each module. (Table 2). Patients in both *ETH* intervention conditions will have the option of enrolling in an educational text messaging service designed to supplement the *ETH* education they are receiving in the mail. Patients in the *ETH*-PG and *ETH*-EG conditions will receive a minimum of 67 messages. Those who respond to interactive messages, such as quiz questions, could receive up to 80 messages over the intervention period. Patients who opt into the text messaging are provided $10 remuneration to cover the cost of standard text messaging rates. Text messaging services are provided through Songwhale LLC, [47] an institutional review board approved partner.

**Table 2 Tab2:** Sample text messages

Text Message Type	Content
Recommendation	What does your family think about living donation as an option for you? Ask them! They know you the best and their opinions might help you decide.
Quiz	Can living donors who donate a kidney still have kids afterwards? Know the answer? Text back YES or NO.
Fact	Did you know? Nationally, most patients wait, on average, 4 years for a kidney from the deceased donor waiting list.

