These studies show support for outreach-based, culturally-compentent educational approaches to be studied and further expanded in the *ETH* RCT described here. However, neither of these studies examined whether their respective interventions were effective when targeted toward low-SES patients. Since these patients may take more time to educate, we do not know whether it is feasible to overcome the greater level of challenges faced by dialysis providers in educating them about transplant.

Upon completion of this investigation, we will have assessed the effectiveness of a program that delivers health education directly to patients’ homes in small, digestible increments. Additionally, we will be able to explore the effectiveness of text messaging as a means of delivering health education to patients within a low-income population. Hopefully, these methods prove to be effective at alleviating staff burden within dialysis centers, educating patients in an engaging fashion, and providing a potentially cost-effective strategy for disseminating transplant education. Furthermore, through this trial, we will have developed an education program that could be delivered directly to patients through a healthcare organization, health insurance company, or other community partners—all organizations that have continued access to patients as a result of the managed care they provide. Next steps will include examining the effectiveness of *ETH* educational approaches with Hispanics, the most rapidly increasing portion of the ESRD population in the United States [1] who may face particular challenges around pursuing transplant [63, 64] and assessing the generalizability of these findings in other regions of the country.

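### The exploratory texting contrast compares patients who chose texts with those who did not, so it can show an association but not the impact of the texts

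*Protocol article*

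**What the plan says.** **What is randomized.** Under Patient Recruitment Eligibility, and Retention, a consenting patient "he or she will be randomized to one of the three educational conditions". Texting is not one of the randomized factors.

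**How texting is assigned.** Under Text Messaging, patients in both ETH arms "will have the option of enrolling in an educational text messaging service". The same section adds: "Patients who opt into the text messaging are provided $10 remuneration". Receiving texts is therefore the patient's own choice.

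**The analysis.** The last sentence of Statistical Analyses states the aim, "we will explore the impact of the text messages", and the method, "by comparing all study outcomes between patients who did and did not enroll in the texting program". The contrast is "stratified by whether the patient was randomized to the" educator-guided or patient-guided arm, and is fitted with multilevel random effects models. No other control is tied to it.

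**The conclusion drawn.** The Discussion says that "we will be able to explore the effectiveness of text messaging as a means of delivering health education to patients" in a low-income population.

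**The concern.** Randomization protects the comparisons among the three conditions. It does not protect a comparison of patients within one condition who sort themselves into texting and no texting. Those without a usable cell phone fall among the non-enrollers, as do those less interested in the topic or less comfortable with reading. These traits may also govern how much a patient learns from the mailed videos and print, so a difference between the groups could arise even if the texts added nothing.

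The contrast covers all study outcomes and is described in terms of impact and effectiveness. The Discussion also looks ahead to delivery of the program through insurers and healthcare organizations. A self-selected difference read as an effect of texting could influence whether texts are kept in such a program.

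**Working it through.** **Step 1. Set the sections side by side.**

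- Assignment: Text Messaging makes enrollment optional. The recruitment section randomizes only the education condition.
- Control for confounding: Statistical Analyses names one stratifier for the texting contrast, the ETH arm. The choice to enroll is made within each arm, so stratifying by arm separates patient-guided from educator-guided patients but leaves the selection untouched.
- Partial protection: the same section analyses knowledge, self-efficacy and decisional balance as change from baseline. That removes a constant difference in level between enrollers and non-enrollers. It does not remove a difference in how fast they learn.
- No such protection: the Decisional Conflict Scale and the three informed-decision items are compared at follow-up only.
- Available covariates: Predictors and Covariates lists age, race, education, cell-phone access, income vulnerability, medical mistrust, prior transplant education and health literacy. None is linked to the texting contrast.

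**Step 2. Illustrate the possible size.** The article gives no enrollment rate and no expected texting effect, so it has no figure to reproduce.

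Inputs:
- From RCT Overview: 150 patients per arm at follow-up.
- Assumed: true text effect zero; two-sided 5% z-test within one ETH arm; share enrolling p = 0.3, 0.5 or 0.7.
- Assumed: an unmeasured trait, such as motivation, has correlation r_e with the propensity to enroll and r_y with the outcome, each from 0.2 to 0.5. For change outcomes, r_y refers to change.
- Center clustering is ignored.

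Formulas, in outcome SD units, with t = z(1 − p):
- gap = φ(t)/p + φ(t)/(1 − p)
- bias d = r_e × r_y × gap
- SE = √[1/(150p) + 1/(150(1 − p))]
- rejection rate = 1 − Φ(1.96 − d/SE) + Φ(−1.96 − d/SE)

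For p = 0.5: gap = 0.399/0.5 + 0.399/0.5 = 1.596, and SE = √(1/75 + 1/75) = 0.163.

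For p = 0.3 (0.7 gives the same values): gap = 0.3477/0.3 + 0.3477/0.7 = 1.656, and SE = √(1/45 + 1/105) = 0.178.

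| p | r_e = r_y | bias d (SD) | d/SE | rejection rate |
|---|---|---|---|---|
| 0.5 | 0.2 | 0.04 × 1.596 = 0.064 | 0.39 | 0.068 |
| 0.5 | 0.3 | 0.09 × 1.596 = 0.144 | 0.88 | 0.142 |
| 0.5 | 0.5 | 0.25 × 1.596 = 0.399 | 2.44 | 0.685 |
| 0.3 or 0.7 | 0.2 | 0.04 × 1.656 = 0.066 | 0.37 | 0.066 |
| 0.3 or 0.7 | 0.3 | 0.09 × 1.656 = 0.149 | 0.84 | 0.133 |
| 0.3 or 0.7 | 0.5 | 0.25 × 1.656 = 0.414 | 2.32 | 0.642 |

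The rejection rate therefore runs from about 7% to about 69%, against a nominal 5%. If either correlation is zero, it stays at 5%.

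**The case against.** The other side has real points.

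- **The analysis is exploratory.** Both the analysis sentence and the Discussion use the verb explore. The contrast is not primary, plays no part in the power calculation, and is absent from the abstract's conclusions. A reader might infer that the article promises a confirmatory causal estimate of texting; it does not. This limits the importance of the point, but exploratory status does not make a self-selected contrast a measure of impact, and the article gives no caveat about self-selection here. It does plan to check selection for refusers and drop-outs.
- **An article leaves covariate lists to the analysis plan.** That is fair, and the mixed models can take covariates. The point therefore does not rest on a missing list. It rests on what is stated: the contrast, its single stratifier and the words used for its result.
- **No data show that enrollers differ.** Correct. A reader might conclude that a spurious difference is bound to appear; the document supports only that one could. The low end of the illustration is barely above nominal.
- **The size is soft.** A reader might multiply the article's 89% household cell access by its 73% texting among owners, get 65%, and take that as the enrollment rate. Those are general access and use figures for the United States, not opt-in rates among low-income dialysis patients. A reader might also turn the bias into knowledge points by back-solving the sample size, assuming a two-sided test: 2.0 × √(150/2) / (2.394 + 1.282) = 4.71. The power section says its calculation allowed for intra-class correlation, so 4.71 absorbs clustering inflation and is not the SD of the change score.

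**Conclusion.** The point holds as a should-fix on a secondary, exploratory analysis. Carried out as written, the texting contrast can be confounded by self-selection within each ETH arm, and it should not be reported as impact or effectiveness. Change scores reduce the problem for knowledge, self-efficacy and decisional balance without removing it. The outcomes compared only at follow-up have no such protection.

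The conclusion follows from the design and does not depend on the illustration. The rejection rates of about 7 to 69% rest entirely on the assumed enrollment, the assumed correlations and a zero true effect, and show only that the distortion could be anywhere from negligible to large. The comparisons among the three randomized conditions are unaffected.

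**What to change.** Keep the contrast, stratified by ETH arm, and change three things.

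1. Adjust, or weight by a propensity score, for the baseline value of the outcome where it was measured, and for variables already collected: cell-phone access, age, race, education, health literacy, prior transplant education, income vulnerability and medical mistrust.
2. Restrict the contrast to patients with a cell phone, so that those who could not have enrolled are not used as the comparison group. The restriction itself then deals with phone access; adjustment for it matters only if an unrestricted version is also shown.
3. In Statistical Analyses and the Discussion, describe the result as a non-randomized association in place of impact or effectiveness.

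Asking all patients before randomization whether they would accept texts may look attractive, but it is not recommended. Among willing patients the texts still come together with the ETH modules, so comparing ETH with control by willingness would not separate the two.

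The cost is a little more modelling, a smaller sample for this contrast and a more modest claim. No new data are needed and the randomization is unchanged. Unmeasured motivation may still bias the adjusted result, which is why the wording must change as well as the model.
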